### Strengths of the Study

This study has several strengths, such as (1) targeted population: focusing on patients with insomnia after SM surgery, a special population with unmet clinical needs, filling the gap in existing research; (2) rigorous study design: adopting a prospective, multicenter RCT design, with strict randomization, allocation concealment, and single-blind methods to ensure the internal validity of the study; (3) comprehensive outcome indicators: combining subjective (PSQI, ISI, etc) and objective (actigraphy) indicators to comprehensively evaluate sleep quality, and simultaneously assessing quality of life and depressive symptoms to reflect the overall therapeutic effect; (4) standardized intervention: the acupoint selection, manipulation methods, and treatment parameters of electroacupuncture are standardized in accordance with STRICTA guidelines, and acupuncturists are trained uniformly to ensure the consistency of treatment; (5) complete SAP: in accordance with SPIRIT guidelines, a detailed SAP is provided, including analysis methods for primary and secondary outcomes, additional analyses, and handling of missing data; and (6) complete safety monitoring: establishing a DSMB to monitor the study process, and recording AEs in detail to ensure the safety of participants.

### Limitations

Despite the rigorous design, this study still has some limitations. First, blinding limitations: although Streitberger placebo needles are used for the sham electroacupuncture group, acupuncturists are aware of the grouping, which may lead to performance bias. However, we have taken measures, such as separate treatment rooms and eye masks for patients to minimize this bias. Second, follow-up period: the follow-up period of this study is 8 weeks, which may not be sufficient to evaluate the long-term efficacy of electroacupuncture. Future studies can extend the follow-up period to observe the sustainability of the therapeutic effect. Third, lack of mechanism exploration: this study focuses on clinical efficacy and safety, and does not explore the underlying mechanism of electroacupuncture in improving sleep. Future studies can combine biological indicators (such as neurotransmitters and cytokines) to explore the mechanism. Fourth, exclusion criteria limitations: the study excludes patients with severe comorbidities, mental disorders, and chronic insomnia disorder, which may limit the generalizability of the results to the entire population with postoperative SM. Fifth, potential confounding factors: although we have adjusted for common confounding factors in the statistical analysis, there may still be unmeasured confounding factors (such as postoperative pain intensity and family support) that affect the study results. Finally, single-blind design: due to the characteristics of acupuncture treatment, it is difficult to implement double-blinding (acupuncturists cannot be blinded). This may introduce potential bias, but single-blinding of patients and outcome assessors can still reduce the impact of subjective factors.

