**Methods:**

This is a study protocol for a randomized controlled trial. We will randomly assign 196 patients with insomnia after spinal metastatic cancer surgery to the acupuncture group (n=98) or the control group (sham acupuncture group; n=98). All participants will be treated on the first day after surgery and receive 12 sessions in total (30 min per session, 3 sessions per wk for 4 weeks). The primary outcome is the change in Pittsburgh Sleep Quality Index score from baseline to post treatment (wk 4). The secondary outcomes include actigraphy records (sleep efficiency, number of sleep awakenings, total sleep time, sleep latency, and wake after sleep onset), Insomnia Severity Index, Spine Oncology Study Group Outcomes Questionnaire 2.0, and Patient Health Questionnaire-9. All results will adhere to the intention-to-treat principle and will be evaluated at baseline, posttreatment (wk 4), and follow-up (wk 12).

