Numerous randomized controlled trials (RCTs) have evaluated the efficacy and safety of electroacupuncture for cancer-related insomnia (CRI), but SM postoperative insomnia has unique characteristics that distinguish it from general CRI. First, the pathogenesis is more complex; SM surgery involves spinal structure reconstruction, which may cause persistent postoperative pain, limited spinal movement, and neurological irritation, all of which directly interfere with sleep initiation and maintenance. In contrast, general CRI is more often associated with systemic symptoms such as tumor-related fatigue, anxiety, and drug side effects. Second, the sleep disturbance pattern is specific; patients with postoperative SM often experience sleep fragmentation due to nocturnal pain and positional restrictions, while general CRI is more likely to present as difficulty falling asleep or early awakening. Third, the rehabilitation context differs; patients with SM are in a critical period of spinal function recovery, and sleep quality directly affects tissue repair and neurological function restoration, whereas general CRI has a more indirect impact on disease progression. These unique characteristics indicate that the efficacy and mechanism of electroacupuncture for SM postoperative insomnia may differ from those for general CRI, justifying the necessity of this targeted study.

Studies in recent years have further confirmed the multifaceted adverse impact of postoperative insomnia on patients with SM. In terms of physical recovery, insomnia can reduce the body’s immune function, inhibit the repair of damaged tissues, and delay the recovery of postoperative motor and neurological functions [11-13]. In terms of disease prognosis, insomnia can up-regulate the expression of cancer-promoting factors (such as IL-6 and TNF-α), increase the risk of tumor recurrence and metastasis, and reduce the overall survival rate of patients [14-16]. In terms of mental health, long-term insomnia is closely associated with anxiety, depression, and other negative emotions, which further aggravates the decline in quality of life [17,18]. A 2023 study by Kim et al [8] found that CRI can mediate the impact of sleep disturbance on disease progression fear in patients with postoperative lung cancer, highlighting the importance of intervening in insomnia.

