#### Inclusion Criteria

First, male or female participants who were aged 18 years or older. This age limit is set because adults have relatively stable physiological functions and can better cooperate with the treatment and evaluation process.

Second, patients diagnosed with SM based on cytological or histopathological features, and undergone SM surgery within 1‐2 weeks. This time interval is determined because sleep disturbance after SM surgery is most prominent within 1‐2 weeks postoperatively, and intervention during this period is more conducive to improving rehabilitation outcomes.

Third, the PSQI score was >11. Patients with chronic insomnia disorder (defined as insomnia lasting ≥3 months before surgery) are excluded. According to the validation study of the Chinese version of PSQI, a score >11 indicates moderate to severe insomnia, which is a reasonable threshold for selecting patients with clinically significant postoperative insomnia [31,32].

Fourth, have an estimated survival period of at least 6 months. This is to ensure that participants can complete the entire treatment and follow-up process, and avoid the impact of patient death on the study results. The survival period is estimated by the attending physician based on the patient’s tumor type, stage, treatment response, and other factors.

Fifth, consent to participation and completion of the full treatment process, and provide written consent.

Sixth, postoperative blood examination showed no obvious abnormality, indicating that the patient’s general condition is stable and can tolerate electroacupuncture treatment.

Finally, no history of shift work in the past 6 months. Shift work can independently affect sleep patterns and confound the study results, so such individuals are excluded.

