##### Spine Oncology Study Group Outcomes Questionnaire 2.0

The Spine Oncology Study Group Outcomes Questionnaire was developed by the Spine Oncology Study Group. In 2018, Versteeg et al [41] further validated the first version of this questionnaire and introduced the revised version, Spine Oncology Study Group Outcomes Questionnaire 2.0 (SOSGOQ 2.0). The revised version (SOSGOQ 2.0) has been extensively used in the literature to determine the effects of SM and its treatment [1,41,42]. Our term successfully verified the cross-cultural adaptation of SOSGOQ 2.0 into simplified Chinese, which demonstrated excellent acceptability, score distribution, internal consistency, test-retest reliability, and validity [4]. Therefore, the simplified Chinese version of the SOSGOQ 2.0 is considered a satisfactory tool for evaluating the health-related quality of life of Chinese patients with SM. The simplified Chinese version of the SOSGOQ 2.0 is composed of 6 health-related quality of life domains with 27 questions and 5 answer options, including physical function (6 items), neurological function (4 items), pain (5 items), mental health (2 items), social function (3 items), and posttherapy (7 items). Posttherapy questions will only be completed if the patient indicates having undergone post treatments for SM. Each question is answered via a 5-point Likert scale from 0 to 4. The overall score is calculated by summing the points of all items and excluding the posttherapy questions, with a maximum score of 80 and a minimum of 0. The higher the score, the worse the quality of life.

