#### Analysis of Primary and Secondary Outcomes (SPIRIT Item 20a)

##### Primary Outcome Analysis

The primary outcome is the change in PSQI total score from baseline (wk 0) to posttreatment (wk 4). ANCOVA will be used to compare the between-group difference in PSQI score changes, with baseline PSQI score, age, gender, tumor type, and participating center as covariates. This method can adjust for potential confounding factors and improve the statistical efficiency of the analysis.

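### Postoperative pain is listed as unmeasured although SOSGOQ 2.0 pain items are collected at week 0; leaving them out of the primary ANCOVA may cost some precision but causes no bias

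*Protocol article*

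**What the plan says.** - **Limitations.** Despite the planned adjustment, the article warns of possible "unmeasured confounding factors (such as postoperative pain intensity and family support".
- **SOSGOQ 2.0.** The domains that enter the overall score are "physical function (6 items), neurological function (4 items), pain (5 items), mental health (2 items), social function (3 items". On scoring: "Each question is answered via a 5-point Likert scale from 0 to 4". The section defines one overall score, from 0 to 80, and no separate pain score.
- **Table 1.** SOSGOQ 2.0 is ticked at week 0 and at each later outcome visit. The Abstract likewise says results "will be evaluated at baseline, posttreatment (wk 4), and follow-up (wk 12". The two differ on the follow-up weeks, but both include a baseline assessment.
- **Inclusion Criteria.** Patients must have "undergone SM surgery within 1‐2 weeks".
- **Introduction.** Surgery for spinal metastasis may cause "persistent postoperative pain, limited spinal movement, and neurological irritation, all of which directly interfere with sleep initiation and maintenance".
- **Primary Outcome Analysis.** The ANCOVA compares PSQI change "with baseline PSQI score, age, gender, tumor type, and participating center as covariates". The section gives two reasons for adjusting: to deal with possible confounders and to gain efficiency.

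**The concern.** Two statements do not fit together. A factor cannot be simply unmeasured when five items on it are scheduled at baseline in every patient. And a model meant to gain efficiency leaves out a baseline variable that the protocol's own account of this insomnia treats as acting directly on sleep, while it includes age, gender and tumor type, for which the article gives no comparable argument.

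At stake is the standard error of the primary treatment effect. A baseline variable that predicts the outcome beyond the other covariates removes residual variance. It also lets the analysis account for a chance imbalance in that variable. Here the data are already scheduled, so the gain, if there is one, needs no extra collection.

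**Working it through.** **Inputs.** Sample Size Calculation: difference 1.8, SD 3.9, two-sided alpha 0.05, 90% power, 20% dropout, 98 per group. The partial correlation r is not in the document; it is an assumption, taken over the range 0 to 0.5.

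**Step 1: the plan's own figure.** n per group = 2 × (1.960 + 1.282)² × (3.9/1.8)² = 98.7, so 99 (100 with the exact t test). Dividing by 0.8 for dropout gives 124 (or 125) per group. The stated 98 therefore matches the requirement before dropout, not after it. That is a separate issue, but it sets the starting point: 98 × 0.8 = 78.4, or about 78 completers per arm.

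**Step 2: is baseline pain held?** Five items scored 0 to 4 give a sum from 0 to 5 × 4 = 20. The items counted in the overall score number 6 + 4 + 5 + 2 + 3 = 20, and 20 × 4 = 80, which agrees with the stated maximum. The pain items are thus a quarter of a total already planned, and their sum can be formed from the recorded answers. Since the inclusion criteria require surgery to have taken place, the week-0 answers are postoperative.

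**Step 3: gain in precision.** Take 3.9 as the residual SD before pain enters. Then

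- residual SD with pain = 3.9 × √(1 − r²)
- SE of the group difference = residual SD × √(2/78)
- power from the noncentral t distribution, two-sided 0.05, difference 1.8

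| r (assumed) | Variance removed (r²) | Residual SD | SE | Power |
|---|---|---|---|---|
| 0 | 0% | 3.900 | 0.624 | 81.7% |
| 0.1 | 1% | 3.880 | 0.621 | 82.1% |
| 0.2 | 4% | 3.821 | 0.612 | 83.2% |
| 0.3 | 9% | 3.720 | 0.596 | 85.1% |
| 0.4 | 16% | 3.574 | 0.572 | 87.8% |
| 0.5 | 25% | 3.377 | 0.541 | 91.1% |

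The normal approximation gives values about half a point higher at most (82.2% at r = 0, 88.2% at r = 0.4). Put as sample size, r = 0.3 is worth 78/(1 − 0.09) = 85.7 completers per arm, about 8 more. At r = 0.4 it is 78/(1 − 0.16) = 92.9, about 15 more.

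**Step 4: bias and type I error.** In 3,000 simulated randomized trials with 78 per arm and r = 0.3, type I error was 4.5% both without and with the pain term. With a true difference of 1.8 in favour of treatment, the mean estimate was −1.81 in both models. Power was 81.9% without pain and 84.9% with it. Only precision changed.

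**The case against.** The planned model is valid as it stands. It contains the baseline outcome and center, which is the stratification factor, and in a randomized trial no further covariate is required. The error rate of the test already allows for chance imbalance in anything left out. All of this stands.

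The gain may also be small. r is conditional on baseline PSQI. If pain acts on sleep as the Introduction says, baseline PSQI already carries part of its effect, and r could be near 0. The SD of 3.9 is given for an unadjusted t test, so treating it as the residual SD after the other covariates is a simplification. The low starting power comes from the sample-size problem, not from the missing pain term. These points stand too; they limit the size of the finding, not its facts.

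Several stronger readings are tempting but not supported:

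- *The treatment comparison is confounded by pain.* Allocation is randomized, so it is not; the word confounding in the Limitations is loose.
- *The protocol says pain cannot be adjusted for.* It says only that unmeasured factors may remain.
- *Pain is the leading cause of insomnia according to the protocol.* The Introduction lists it beside restricted movement and neurological irritation, without ranking.
- *A pain-domain score is already defined.* Only the overall score is. The wording of the items is not shown either, so they may not equal a dedicated intensity scale. That supports a narrower limitation, but not the word unmeasured.
- *The imputation and secondary models must change as well.* The imputation model already takes in secondary outcomes and baseline characteristics, and the SOSGOQ 2.0 ANCOVA already adjusts for its own baseline, which contains the pain items.

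**Conclusion.** The point holds in a limited form and is minor. The limitation is inaccurate against the trial's own schedule: pain is captured at week 0 through five SOSGOQ 2.0 items. The primary ANCOVA leaves out a baseline value that the protocol's own reasoning suggests is prognostic. The consequence is possible loss of precision only. With 78 completers per arm, adding the value moves power from about 82% to between about 82% (r near 0) and 88% (r = 0.4).

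This rests on three assumptions: the value of r, which no part of the document supplies; 3.9 as the residual SD before pain enters; and a postoperative baseline, as the inclusion criteria imply. The Abstract's statement that treatment is given on the first day after surgery does not fit those criteria, and the two passages must be reconciled.

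**What to change.** 1. Before unblinding, prespecify the sum of the five week-0 SOSGOQ 2.0 pain items (0 to 20) as an additional covariate in the primary PSQI ANCOVA. The article says the detailed analysis plan is still to be written before data lock and unblinding, so one line there is enough.
2. Reword the Limitations to say that pain is captured only through the SOSGOQ 2.0 pain items. Family support is not touched by this point.
3. Leave the imputation model and the SOSGOQ 2.0 secondary ANCOVA as they are.

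The cost is one degree of freedom and two short edits, with no new data. If r turns out near 0, almost nothing is lost. Adding the covariate after unblinding would be post hoc, so it should be settled beforehand.

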### Future Directions

If the efficacy of electroacupuncture is confirmed in this study, future research can be carried out in the following directions: (1) optimize the treatment plan: explore the optimal acupoint combination, treatment frequency, and course of electroacupuncture for SM postoperative insomnia to further improve the therapeutic effect; (2) mechanism research: explore the mechanism of electroacupuncture in improving SM postoperative insomnia from the perspectives of neuroendocrinology, immunology, and circadian rhythm; (3) combined therapy: study the efficacy of electroacupuncture combined with other nonpharmacological therapies (such as cognitive behavioral therapy for insomnia and music therapy) in the treatment of SM postoperative insomnia; (4) expand the population: conduct studies in patients with SM with different tumor types, surgical methods, and disease stages to further verify the generalizability of the results; (5) long-term follow-up: extend the follow-up period to 6‐12 months to evaluate the long-term efficacy and safety of electroacupuncture; (6) individualized treatment: based on patient characteristics (such as age, gender, and tumor type), develop individualized electroacupuncture treatment plans to improve the precision of treatment.

### Dissemination Plan

The results of this study will be disseminated through multiple channels. First, academic conferences present the study results at domestic and international conferences on Traditional Chinese Medicine, oncology, and sleep medicine to exchange with peers. Second, academic journals publish the study results in high-quality peer-reviewed journals to provide evidence for clinical practice guidelines. Third, clinical promotions popularize the effective treatment plan among clinical doctors in relevant fields (such as orthopedics, oncology, rehabilitation, and Traditional Chinese Medicine) through training courses, workshops, etc, to benefit more patients with insomnia after SM surgery. Fourth, by public education, the research results are disseminated to the public through hospital official websites, WeChat (Tencent Holdings Limited) public accounts, and other platforms to improve the awareness of nonpharmacological therapies for insomnia. Finally, by providing policy recommendations to health administrative departments based on the study results, promoting the inclusion of electroacupuncture in the clinical management guidelines for SM postoperative insomnia.

This study will fill the methodological deficiencies of current clinical trials on acupuncture for the treatment of insomnia after SM surgery and provide a promising therapeutic intervention for clinical patients with insomnia after SM surgery.
